## Methods

### Study design

This is a randomized wait-list control trial that will evaluate the effectiveness, feasibility and acceptability of online CRAFT with a parallel group. Participants will be randomised to receive either online CRAFT for 6 sessions over 6 to 10 weeks or to a wait-list control group who are provided with CRAFT related reading materials during the waiting period. Outcomes will be assessed at baseline and then at 6- and 15-weeks post baseline. Outcome measures will be completed online independently of researchers or clinicians. The trial reporting will comply with CONSORT guidelines. Figure 1 provides an overview of the trial recruitment and process.

**Fig. 1 Fig1:**
[figure not shown]
CONSORT diagram

### Eligibility criteria

Eligible participants will be 18 years or older with a relative or loved one who has a substance problem with or without another mental health condition. Participants must live in a rural area (Modified Monash Model 2–7), have a minimum of weekly contact with their loved one, willing to attend at 6 online counselling sessions, access to a computer with internet or mobile phone with video conferencing capabilities and able to provide informed consent. Exclusion criteria includes domestic and family violence from the person with substance dependence to the participating family member and/or current participation in family support/therapy programs related to substance use.

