# Study protocol for the family empowerment program: a randomized waitlist-controlled trial to evaluate the effectiveness of online Community Reinforcement and Family Training (CRAFT) on the wellbeing of family members with a relative experiencing substance dependence and mental illness

**DOI:** 10.1186/s12888-023-05487-0

**Published:** 2024-01-10

**Keywords:** Rural, Substance disorder, Online therapy, Community reinforcement and family training, Family, Mental health

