In Australia, one in three individuals with a substance use disorder also has a mental health disorder [6]. Two or more conditions are so common among those experiencing mental health or substance use problems that “comorbidity is seen as the rule rather than the exception” [10]. Further, comorbidity results in a greater care burden on the family and increased family conflict compared to single disorders [11–13]. However, very often the presence of co-occurring conditions excludes people from participating in clinical trials and the efficacy of interventions for people with more than one condition is unknown [14].

The aim of the current study is to implement and evaluate Community Reinforcement and Family Training (CRAFT) delivered online by trained counsellors to people living in rural Australia. CRAFT is an evidence-based approach that helps families to reduce a relative’s substance use, engage in treatment, and improve family wellbeing through structured, personalised training and support [2, 15–17]). However, CRAFT is not available in Australia and has limited evidence for mental illness and substance use combined [12]. Derived from Cognitive Behavioural Therapy (CBT) and Motivational Interviewing (MI), the aims of CRAFT are to teach family members how to remove positive reinforcement for problematic substance use behaviour effectively and safely, increase positive reinforcement for non-using behaviour, and help the person with problematic substance use to enter, or be retained in, treatment [18]. In addition, CRAFT aims to improve family members’ social and emotional wellbeing.

In this iteration, CRAFT will be delivered as The Family Empowerment Program, emphasizing family members as the primary target group for the study and aiming to establish CRAFT as a family-focused therapy program in Australia. The study will generate the first Australian outcome data, which will complement the USA outcome data [12] and the Australian adaptation and acceptability data from the team’s previous work [16, 19]. This research project can inform future health system policy on the provision of virtual care for rural Australian families of people with substance dependence and mental illness.

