### Objectives of the study

This trial will determine the effectiveness of an online delivered CRAFT counselling intervention for improving the well-being of family members with a loved one experiencing substance problems with and without co-occurring mental health problems. It is hypothesised that CRAFT implemented online by accredited therapists will be more beneficial than CRAFT self-help information provided to the wait-list group. Compared to the wait-list control group, the CRAFT group will show significant decrease in self-reported levels of depression, anxiety and stress and significant increase in life satisfaction and that these improvements will be maintained over a three-month period post intervention.

It is hypothesized that 1) improvements in depression, anxiety and stress scores as a function of CRAFT relative to the control group will be mediated by: a) acceptability of receiving support online and b) ease of access. Given the lack of information regarding implementation parameters of substance use interventions for families of people with a mental health condition, qualitative methods will explore the experiences of study participants as well as clinicians delivering the program. The study has the following specific aims:

Aim 1: determine the effectiveness of an online delivered CRAFT counselling intervention on on self-reported levels of depression, anxiety, stress and life satisfactionAim 2: qualitatively examine the paricipants’ experiences about the acceptability of receiving support onlineAim 3: qualitatively examine the clinicians’ experiences of delivering the program and feasibility

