### Demographics

Age, gender, ethnicity, living arrangements, financial support, years of education, relationship status and relationship to the relative, mental health diagnosis of relative will be collected.

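### The title and policy aim name families of people with both substance dependence and mental illness, but the trial enrols with or without mental illness, so the pooled effect alone does not speak for the named group

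*Protocol article*

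**What the plan says.** The Protocol article describes its population in two ways.

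**Narrower.** The title refers to "family members with a relative experiencing substance dependence and mental illness". The Background says that CRAFT "has limited evidence for mental illness and substance use combined" and that the project can inform policy on "virtual care for rural Australian families of people with substance dependence and mental illness".

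**Broader.** Objectives of the study refers to families with "a loved one experiencing substance problems with and without co-occurring mental health problems". Eligibility criteria matches this and requires "a relative or loved one who has a substance problem with or without another mental health condition". It requires neither mental illness nor dependence, and the article sets no minimum share of comorbid relatives.

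On the variable that separates the two populations, Demographics states that "mental health diagnosis of relative will be collected", without saying when. Recruitment and follow-up procedures describes a telephone screen against the eligibility criteria, then verbal consent, then randomisation, and only then the link to written consent and the outcome measures. Randomisation and blinding likewise places allocation before the baseline measures.

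**The concern.** A reader of the title will take the trial's main result as evidence about families who face both conditions. The result will come from a mixture in which that group has an unknown share. The Background reports that comorbidity brings more care burden and more family conflict. Both bear on the family member's distress, which the trial measures, so a different effect in the two groups is plausible, though the article does not claim one. If the effects differ, a favourable pooled result could come mostly from families outside the title's population and still be cited for those inside it, or the reverse.

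The second issue is the quality of the variable. Mental illness is not needed to qualify, so the screen need not record it. If it is first recorded with the baseline forms, it is reported by people who already know whether they start within 7 days or within 6 weeks, and it is missing for anyone randomised who never completes those forms.

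**Working it through.** **1. The plan's own figure.** Sample size calculation gives 216 (108 per group) for 29% against 15%, 5% significance and 80% power. With p̄ = 0.22, the pooled-variance formula is

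n per arm = [z_α·√(2 × 0.22 × 0.78) + 0.8416·√(0.29 × 0.71 + 0.15 × 0.85)]² / 0.14²

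- One-sided (z_α = 1.645): (0.9636 + 0.4860)² / 0.0196 = 107.2, so 108 per arm and 216 in all. This matches.
- Two-sided (z_α = 1.960): (1.1482 + 0.4860)² / 0.0196 = 136.3, so 137 per arm and 274 in all.

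The 260 is 216 × 1.2 = 259.2, rounded up. All of this concerns the pooled sample and treatment engagement. Nothing in it sizes the comorbid group. The sidedness and the choice of outcome are separate matters.

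**2. Size of the named population.** The document gives no expected mix. The Background's figure, that "one in three individuals with a substance use disorder also has a mental health disorder", is a general Australian one, so I take one third as one end of an assumed range and two thirds as the other. For share s of 216 analysed, n per arm = 216 × s / 2.

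**3. Precision for a continuous wellbeing score, in SD units.** Two-sided 5%, 80% power, unadjusted comparison at one time point:

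- detectable difference = (1.960 + 0.842) × √(2/n per arm)
- 95% CI half-width = 1.96 × √(2/n per arm)

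| Population | n per arm | Detectable difference | CI half-width |
|---|---|---|---|
| Comorbid, s = 1/3 | 36 | 0.66 | 0.46 |
| Comorbid, s = 1/2 | 54 | 0.54 | 0.38 |
| Comorbid, s = 2/3 | 72 | 0.47 | 0.33 |
| All analysed | 108 | 0.38 | 0.27 |

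If 20% of 260 are lost, 208 remain. At s = 1/3 that is 34.7 per arm, with a detectable difference of 0.67 SD and a half-width of 0.47 SD. Adjustment for baseline would narrow every row. If it does so by a similar factor throughout, the ratios hold: at s = 1/3 the comorbid interval is √3 = 1.73 times as wide as the pooled one.

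**4. What the pooled effect leaves open.** Roughly, pooled effect = s × (effect in comorbid) + (1 − s) × (effect in the rest). As an illustration, a pooled difference of 0.38 SD with no effect in comorbid families needs 0.38 / (2/3) = 0.57 SD in the rest at s = 1/3, and 0.38 / (1/3) = 1.14 SD at s = 2/3. The first is not far-fetched; the second is much less so. How far the pooled figure constrains the comorbid effect depends on the mix, which is unknown.

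**5. Comparing the two groups.** The detectable difference between the two subgroup effects is 2.802 × √(4/(216s) + 4/(216(1 − s))): 0.81 SD at s = 1/3 or 2/3, and 0.76 SD at s = 1/2. A powered interaction test is out of reach, so estimation is the realistic aim.

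**6. Would stratified randomisation help?** Take 87 comorbid relatives among 260 (s = 1/3) under simple 130:130 allocation, which is an assumption. The number in one arm has SD √(130 × 0.335 × 0.665 × 130/259) = 3.8, so a 36 v 51 split is at the edge of the 95% range. Its SE factor is √(1/36 + 1/51) = 0.218, against √(2/43.5) = 0.214 when balanced, about 1.5% more. The width comes from the size of the subgroup, not from imbalance.

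**The case against.** The best defence is that the design does what the objective asks. Objectives of the study covers relatives in both situations, Eligibility criteria enrols them, and the pooled effect answers that question. The Background also argues from rural service scarcity and from CRAFT being unavailable in Australia. It complains that comorbidity keeps people out of trials, and inclusive eligibility is a fair response to that. All of this stands. The mismatch is between title and policy aim on one side and objective and eligibility on the other.

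A reader might infer more, and the article does not support it:

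- **That the trial cannot answer for comorbid families at all.** The diagnosis is collected, and randomisation supports a comparison within that subgroup without stratification. The limit is precision.
- **That about two thirds of the sample lies outside the title's population.** This applies a general figure to a self-selected sample. The Background also calls co-occurrence the norm, and recruitment runs partly through healthcare and treatment agencies.
- **That the diagnosis is recorded after allocation.** This is a fair inference from the sequence, but Demographics gives no timing. Nor is a participant's start date likely to change a diagnosis the relative already has; the likelier harm is missing values.
- **That the randomisation is unstratified, or that no subgroup analysis is planned.** A condensed article may leave both to the full protocol or analysis plan, so silence on them is not an error.

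That the effect differs by comorbidity is also unproven: the Background reports greater burden, not a different response to CRAFT.

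**Conclusion.** The inconsistency is on the face of the article and needs nothing from an unseen analysis plan. The title and the policy aim claim a narrower population than the objective and the eligibility criteria define. The pooled effect is valid for the broader one. Taken alone, it is not evidence for families of people with both conditions.

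For an assumed comorbid share of one third to two thirds of 216 analysed, the named group is 36 to 72 per arm, with a detectable difference of 0.66 to 0.47 SD against 0.38 SD pooled. These figures assume equal arms and no baseline adjustment, and they shift with the real mix. They show that a subgroup estimate is feasible but imprecise, not that it is worthless. The point about timing is conditional: it matters only if the diagnosis is indeed first recorded after allocation.

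**What to change.** 1. In the results report, word the title and conclusions for the population enrolled: families of a person with a substance problem, whether or not that person also has a mental health condition. This also settles the difference between dependence in the title and a substance problem in the criteria.
2. Add one yes/no question on the relative's mental health condition to the existing telephone screen, so that it is known before allocation for everyone randomised. Recruitment began in October 2023, so add it from the amendment onward. For those already randomised, use the diagnosis collected and report when it was recorded and how often it is missing.
3. Include this status as a covariate in the mixed model. Report the CRAFT-minus-control difference with 95% CI by status, and the difference between the two, as estimation and not as a powered test.
4. Base any statement about comorbid families on their own estimate.

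Stratifying the randomisation list on this status is optional and adds little precision. The cost is one screening question, a few extra lines of results and some rewording. The drawback is a wide interval for the comorbid group, with a half-width near 0.47 SD if one third are comorbid and 208 are analysed.

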### Recruitment and follow-up procedures

Participants will be recruited from any rural areas in Australia by advertisements through healthcare and substance treatment agencies and health advice internet sites, in local newspapers and radio stations and paid geo-located (rural) social media advertisements (see Supplementary Material). The advertisement will include information about CRAFT, highlighting that the program’s goals are to improve the participants’ mental health and increase the likelihood of their relative’s engagement in treatment. Individuals who are interested in participating will register on a secure website or by contacting the study coordinator.

Those who are registered will be contacted within 48 h and invited to complete a short telephone screen using the inclusion and exclusion criteria. If eligible, the study information and process will be described, and verbal consent will be gained. Following this, participants are randomised to either the waitlist or intervention group, and a first initial appointment is organised with an in-community CRAFT practitioner. Participants will then be sent a link to the written consent form and outcome measures.

On average, the information and screening process will take approximately 20–30 min to complete. Once the consent is signed, the participant can access the online baseline measures for completion. If the measures are not completed, SMS reminders will be sent after 2 days. If the participant still does not complete the measures, they will be contacted by phone to confirm their intent to join the study and to ensure that they can access the survey. Participants who complete all three surveys (baseline, 6 and 15 weeks) will receive $120AUD in gift card for their time and participation. Individuals who have not responded to the initial call or have not completed the follow-up measures will be contacted on a weekly basis by both phone and SMS for up to 4 weeks after the follow-up is due.

### Randomisation and blinding

The randomisation procedure for this project will be conducted by an independent researcher ([name]) using STATA software (Version 18 MP) and with the 'randomizr' package. This researcher will not be involved in other aspects of project implementation, such as CRAFT delivery or data collection. The researcher (NS) who recruits the participants will have no access to the order of allocation. All participants will be allocated an identification number and, before completing their baseline measures, will be randomly allocated to either the CRAFT group or the wait list control group. Individuals randomized to the control group will be assigned a 6-week wait time.

All assessments are conducted online, thus minimizing the possibility of researcher bias. Analysis of results will be blinded to the clinicians delivering CRAFT. The clinicians will be provided with contact information of consenting participants and they will deliver the program as scheduled without knowing which group the person is allocated to. Trial participants will be informed their start date for the intervention as 1. as soon as possible (Group A—within 7 days) or 2. within 6 weeks (Group B—WLC) without being informed which group they are in. The need for unblinding is not anticipated.

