#### Statistical analysis

This study will employ a three-stage analytical approach. In the first stage, baseline characteristics of study participants will be identified using descriptive statistics and standard deviations [30]. The second stage involves bivariable analysis using the chi-square test for categorical variables and the t-test for continuous variables, including the estimation of differences in proportion and mean (difference-in-difference) between intervention groups [30]. To assess the intervention's effects on primary outcomes, mixed effect regression modelling will be applied. Intervention effects will be quantified using mean differences (MD) for continuous variables and relative risks (RR) for categorical variables, along with their corresponding 95% confidence intervals (CI) [31]. The primary results will be based on adjusted effect measures, and all analyses will adhere to the intention-to-treat (ITT) principle [32]. STATA version 18 will be used for the analyses, and statistical significance will be declared by *p*-values < 0.05.

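### Randomisation and appointment booking come before written consent and baseline, so self-rated baseline is probably completed with the arm known and people can leave after allocation without giving data

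*Protocol article*

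**What the plan says.** Recruitment and follow-up procedures sets out the order after the telephone screen. First: "If eligible, the study information and process will be described, and verbal consent will be gained". Next, "participants are randomised to either the waitlist or intervention group, and a first initial appointment is organised with an in-community CRAFT practitioner". Only after that: "Participants will then be sent a link to the written consent form and outcome measures". The survey is gated on the signature: "Once the consent is signed, the participant can access the online baseline measures for completion". Those who do not complete it get an SMS after 2 days; if that fails, "they will be contacted by phone to confirm their intent to join the study".

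Randomisation and blinding confirms the order: each participant has an identification number and, "before completing their baseline measures, will be randomly allocated to either the CRAFT group or the wait list control group". The same section says "Trial participants will be informed their start date for the intervention", either within 7 days (Group A) or within 6 weeks (wait list), with the group name withheld. It presents this as blinding.

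Statistical analysis uses a difference-in-difference at its second stage, then mixed-effects regression with adjusted effects as the primary results, and adds that "all analyses will adhere to the intention-to-treat (ITT) principle". Sample size calculation allows 20% attrition, described as loss during follow-up.

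**The concern.** A baseline measured before allocation cannot be affected by it. Here allocation comes first, and the information participants receive separates the arms. Someone who has had the study process explained and is then given a six-week wait can work out which arm that is. DASS-21, the Satisfaction with Life Scale and the Flourishing Scale are self-rated, so hope, disappointment or relief on learning the start date can move the baseline score. Completing the survey online guards against researcher influence but not against this.

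Two further consequences follow from the same order:

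- No stated rule requires baseline before session 1, so a late Group A baseline could follow the start of treatment.
- The point at which people commit in writing falls after randomisation. Those who do not sign, or who say on the phone that they no longer wish to join, are randomised people with no data, and their numbers may differ by arm. Hiding the sequence from the recruiter does not prevent this, because the loss arises after allocation.

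**Working it through.** **Order of events, from the two sections together**

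1. Telephone screen and verbal consent.
2. Randomisation, with a first appointment organised.
3. Link to written consent and measures sent.
4. Written consent signed, which opens the baseline survey.
5. Baseline completed, prompted by SMS after 2 days and then by a phone call with no stated deadline.

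Group A starts within 7 days. Nothing elsewhere in the article reverses steps 2 to 5. The date of the start-date notice is not given; since the appointment belongs to step 2, notice before step 5 is the likely reading.

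**The plan's own sample size**

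Inputs from Sample size calculation: 29% v 15%, α 5%, power 80%, 216 in total, 20% attrition, 260 recruited. With pooled variance, n per arm = [z_α√(2 × 0.22 × 0.78) + 0.842√(0.29 × 0.71 + 0.15 × 0.85)]² / 0.14².

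- One-sided 5% (z = 1.645): 108 per arm, 216 in total, as stated. Two-sided 5% (z = 1.960): 137 per arm, 274 in total.
- 216 × 1.2 = 259.2, which rounds up to the stated 260.
- 260 × 0.8 = 208, or 104 per arm.

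The sidedness is a separate matter. Only the 104 per arm is used below.

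**Detectable difference on a continuous outcome** (assumed: two-sided 5%, 80% power, 104 per arm)

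- Unadjusted: (1.960 + 0.842) × √(2/104) = 2.802 × 0.1387 = 0.39 SD. A change score at correlation r = 0.5 gives the same value, because its variance is 2(1 − 0.5) = 1.
- Baseline-adjusted at r = 0.5: SE = √(0.75 × 2/104) = 0.120, and 2.802 × 0.120 = 0.34 SD.

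**Effect of a baseline shift s between arms** (assumed 0.1 to 0.3 SD)

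- Difference-in-difference: bias = s = 0.1 to 0.3 SD; 0.1/0.39 = 26% and 0.3/0.39 = 77% of the detectable difference.
- Baseline-adjusted: bias = r × s = 0.05 to 0.15 SD at r = 0.5, about 15% to 45% of 0.34 SD. With no true effect, bias/SE is 0.42 to 1.25, and the two-sided type I error rises from 5% to about 7% to 24%.
- At r = 0.7, the adjusted bias is 0.07 to 0.21 SD and the type I error about 11% to 56%.

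**Effect of loss between randomisation and baseline** (rates assumed; 130 per arm, followed by the planned 20% attrition)

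| Loss before baseline, CRAFT v wait list | Left at follow-up |
|---|---|
| 0% v 0% | 104 v 104 |
| 5% v 5% | 99 v 99 |
| 5% v 15% | 99 v 88 |
| 10% v 30% | 94 v 73 |

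If those lost differ from those retained by g SD, the bias is g × (difference in loss rates). For g of 0.25 to 0.5 and a difference of 5 to 20 points, this runs from 0.25 × 0.05 = 0.0125 SD to 0.5 × 0.20 = 0.10 SD.

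**The case against.** The best defence is that much of the harm is inferred. Several parts of it stand.

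- **When participants learn the start date.** The article does not say. Disclosure before baseline is probable from the booking order, but it is not stated.
- **Baseline after session 1.** The SMS and the call can both fall inside the 7 days. Clinicians receive contact details of consenting participants, which may mean that written consent gates the first session. Verbal consent is also consent, so the wording does not settle it. A late baseline is possible, not shown.
- **Analysis.** Difference-in-difference belongs to the second stage. The primary mixed model has adjusted effects whose covariates are not listed. If baseline plays no part in that model, the bias by this route is zero; the loss of randomised people remains. The direction of any bias is also open.
- **Sizes.** The shift, the correlation and the loss rates are all assumptions, and the article gives no detectable difference in SD units.

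A reader might go further in three ways that the article does not support. One is that clinicians are unblinded too: the article reports the start-date message as going to participants, and says that clinicians deliver as scheduled without knowing the group. Another is that the ITT analysis is already broken: the article states a principle, not an analysis set, and the handling of randomised people without consent or baseline may be defined in an analysis plan that is not shown. The third is that people are randomised without consent: verbal consent does come first.

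None of this alters the stated order. It is a procedure written into the protocol, not a detail left for later.

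**Conclusion.** The point holds in this limited form. The article places randomisation and appointment booking after verbal consent but before written consent and baseline. A start within 7 days against a six-week wait in effect tells participants their arm, so the self-rated baseline is probably not independent of allocation. The order also lets people leave after randomisation with no data, possibly unevenly by arm. That threatens the ITT principle, and the 20% allowance, which covers follow-up only, does not provide for it.

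The size is unknown. Under the assumptions shown, the bias from a baseline shift could be trivial or could approach the difference that the trial can detect. The bias from uneven loss is smaller, up to about 0.10 SD. The case for correction does not depend on these figures: no later analysis can fully restore a baseline measured with the arm known, or data from people who left before giving any.

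**What to change.** **New participants.** Use this order: screen, written e-consent, submitted baseline survey, release of the allocation by the independent researcher, then booking of the appointment.

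**Participants already randomised under the present order.** The article says the study commenced in October 2023, so there may be some. Analyse all randomised, report losses before baseline by arm, flag baselines dated after session 1, and report a sensitivity analysis by enrolment procedure.

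**Blinding text.** Replace the claim that participants do not know their group with a statement that they can infer it from the start date and that outcomes are self-reported.

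**Cost.** A change to the online trigger and an ethics amendment; the surveys are already online and the independent randomiser is already in place. The trial would contain two enrolment procedures. Some people will not complete baseline and so will not be randomised. Those who would have refused on hearing of the wait will by then have signed and given baseline data, so they become a visible, reportable loss.

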#### Trial duration

The study has commenced in October 2023 and the recruitment will continue until November 2024. A preliminary analysis will be conducted after 20 participants have completed the program to assess for futlity. If no improvements in participant well-being are found, or wellbeing deteriorates or adverse events are reported the trial will be discontinued. This decision will be made by the research team collaboratively.

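### The only stated blinding of the analysis covers the clinicians, and nothing stated separates the 20-completer outcome look from those who go on recruiting and analysing

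*Protocol article*

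**What the plan says.** Under Randomisation and blinding, the protocol article makes one statement about masking the analysis: "Analysis of results will be blinded to the clinicians delivering CRAFT". Of the same clinicians it says "they will deliver the program as scheduled without knowing which group the person is allocated to". An independent researcher generates the allocation, and "This researcher will not be involved in other aspects of project implementation, such as CRAFT delivery or data collection". The recruiter cannot see the allocation order. On assessment the article says "All assessments are conducted online, thus minimizing the possibility of researcher bias", and the section closes with "The need for unblinding is not anticipated".

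Under Trial duration, "A preliminary analysis will be conducted after 20 participants have completed the program to assess for futlity". The trial is to be discontinued if wellbeing fails to improve, if it worsens, or if adverse events are reported; "This decision will be made by the research team collaboratively".

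Ethics and data monitoring dispenses with a data monitoring committee, citing the trial's small scale, short duration, population and known safety profile. The Abstract names family members' wellbeing as the primary outcome. The Background describes the program as "aiming to establish CRAFT as a family-focused therapy program in Australia".

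**The concern.** A statement about blinding the analysis should protect the steps at which knowledge of arms or results can steer a choice: the decision to continue, the handling of recruitment afterwards, and the final modelling. The stated safeguard covers none of these, because it concerns people who deliver the program.

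The article also fixes a look at primary-outcome results part-way through recruitment, gives the resulting decision to the team that wants to establish the program, and names no one independent to stand between the figures and that team. The remark that unblinding is not expected to be needed does not mention this look.

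What is at stake is the credibility of the stopping decision and of later choices. Anyone who has seen early wellbeing results may be influenced by them, in dealing with new participants or in settling analysis details that are still open. Here the people who may have seen them are those who carry on with the trial.

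**Working it through.** The plan gives no figure on this point to reproduce. The check is a comparison of sections, followed by one illustration.

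**Who is protected from what**

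- Clinicians: kept from the analysis and, as stated, from allocation. Randomisation and blinding gives them delivery, and Treatment fidelity and feasibility gives them session summary sheets. That they do not analyse is inferred from these roles.
- Recruiter: has no access to the allocation order. Nothing is said about access to interim outcome results.
- Randomising researcher: separate from delivery and data collection. Given no part in the preliminary analysis.
- Participants' questionnaires: completed online without researchers or clinicians (Study design). This protects data collection, not the analysis.
- Whoever runs the preliminary look, and the final analyst: no masking stated. Statistical analysis names methods and software only.
- Research team: decides on stopping from wellbeing results and adverse events. No committee stands in between.

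**Would a pooled look hide the arms?**

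Inputs from the article: 260 to be recruited; recruitment from October 2023 to November 2024, taken as about 13 months; CRAFT starts within 7 days (mean taken as 0.5 week); wait-list starts after 6 weeks; program lasts 6 to 10 weeks (mean taken as 8). Assumptions: even accrual, 1:1 allocation, no dropout, and program completion meaning the end of the sessions.

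1. Recruitment period: 13 × 52/12 = 56.3 weeks. Accrual: 260/56.3 = 4.615 per week, or 2.308 per arm per week.
2. Mean time from enrolment to completion: CRAFT 0.5 + 8 = 8.5 weeks; wait-list 6 + 8 = 14 weeks. The gap is 5.5 weeks.
3. Once both arms are producing completers, CRAFT is ahead by 2.308 × 5.5 = 12.7 participants.
4. Of the first 20: CRAFT (20 + 12.7)/2 = 16.3 and wait-list 3.7, so about 82% are CRAFT.
5. Timing T in weeks: 2.308 × [(T − 8.5) + (T − 14)] = 20, so T = 15.6. By then 4.615 × 15.6 = 72 are enrolled, and 260 − 72 = 188 are still to come.

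A simulation with random arrivals and program lengths spread over 6 to 10 weeks gave a mean CRAFT share of 81%, with a 5th to 95th percentile range of 65% to 95%. Fixing the length at 6 or at 10 weeks gave 82%.

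The result depends on accrual. At half the assumed rate the lead is 1.154 × 5.5 = 6.3, and the share is (20 + 6.3)/2 = 13.2 of 20, or 66%. At twice the rate the calculated lead (25.4) exceeds 20, so nearly all would be CRAFT. If completing the program meant returning the 15-week survey, which is timed from baseline in both arms, the imbalance would largely disappear.

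**The case against.** The strongest reply is that a journal article need not describe masking of the analyst; that may sit in a full protocol or analysis plan not shown here. This stands. A reader might infer that the analyst is unmasked, and the article does not show it.

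Second, the clinician sentence can be read as keeping results from those delivering the program, which is a legitimate safeguard. That also stands. The sentence is not false; it simply does no work for the analysis, and it is the only analysis blinding stated.

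Third, Trial duration assigns the decision to the team but does not say who runs the look, whether it is by arm or pooled, or whether the recruiter or final analyst sees figures. A reader might infer that the recruiting team will see results by arm. The text does not say so. A pooled look made up mostly of CRAFT completers would show change within that arm rather than the difference between arms. Even so, the stated rule cannot be applied by the team without some knowledge of wellbeing results, and no restriction on that knowledge is given.

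Fourth, online self-completion and the hidden allocation order limit the ways in which team knowledge could alter the data. This reduces the risk, but does not cover the stopping decision or later analysis choices.

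Finally, a reader might want to attach an inflated false-positive rate, for example from choosing freely between week 6, week 15 and their average. That would measure an unfixed primary visit, not missing masking. Two-sided test statistics are the same whether the arms are labelled or coded, so coding would not cure it. Stopping only for futility does not inflate the type I error either.

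**Conclusion.** The point holds in limited form, with medium confidence. The one stated blinding of the analysis covers people with no described analysis role. The article also fixes a mid-recruitment decision on primary-outcome results by the research team, without a monitoring committee and without a stated firewall. These are features of what the article lays down, not details merely left out.

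The size is qualitative. The illustration shows only that pooling may not hide much: about four in five of the first 20 completers from CRAFT (about two in three at half the assumed accrual), with most recruitment still ahead. It rests on even accrual, no dropout, a full six-week wait and the session-based reading of completion. It does not establish that anyone is unmasked or that the trial's error rate is affected. This is a worthwhile and inexpensive improvement, not a fault that invalidates the design.

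**What to change.** **Trial duration.** State that the independent randomising researcher runs the preliminary outcome analysis and gives the team only a continue/stop recommendation. Withhold the outcome results from the recruiter, the counsellors and the final analyst until data lock. Leave adverse-event reporting to the team and the ethics committee as it is.

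**Randomisation and blinding.** Amend the sentence that keeps that researcher out of other aspects of the project, since it would otherwise conflict with the new task. Add that the final analyst works with neutral arm codes, in a dataset without session-attendance data, because sessions recorded by week 6 would reveal the arm when controls are still waiting. Release the key only after data lock and after the primary model is fixed. The sentence on clinicians can stay as a safeguard for delivery, worded so that it is not taken for masking of the analyst.

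**Cost.** A change of wording and some added work for a researcher already in the trial; no treatment, visit or sample size changes. The team does not see interim outcome figures and must rely on one person's recommendation for that part of its decision. The independent researcher's role becomes wider. Arm coding masks direction only; it does not replace fixing the primary visit and model in advance.
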